### Study design and setting

To test the research hypotheses, a randomised, controlled, multicentre, prospective longitudinal study with three arms is being conducted. Recruiting for the StudyKuS began in 2017 in three different regions in Germany: a) the Erlangen/Nuremberg/Fuerth region (metropolitan region of three cities), b) the Weyarn region (rural area surrounding Munich), and c) the Berlin (capital) region. Each intervention is being carried out by two therapists (with the exception of the EP, which is supervised by the study’s headquarters) over a period of 10 weeks in groups with a maximum of 11 participants. All of the three interventions in one region are taking place during the same time period and are being conducted in consecutive waves – with four waves in the Erlangen/Nuremberg/Fuerth region as well as the Weyarn region and two waves in the Berlin region. Participants in one region and one wave are randomly allocated to one of the three groups (BPT, CBT or EP). Data are being collected via computer-assisted telephone interviews (CATIs) before and directly after the intervention as well as three, six, and 12 months after the treatment. A data monitoring and safety board (DMSB) is established ([name]) and supervises study conduction and severe adverse events (SAEs). All procedures have been approved by the Friedrich-Alexander-Universität Erlangen-Nürnberg Ethics Committee (Ref. 360_16 B). The participant timeline is presented in Fig. 1. Trial Registration Data are presented in Table 1 (ISRCTN12457760, Registration date: 26 July 2017, registered retrospectively).

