#### Exercise program (EP)

The home-based Exercise Program consists of a 20-min physical training program, which addresses the same muscles used in bouldering or climbing. At the beginning of the intervention, all participants receive a training manual (including instructions and explanations of all of the exercises), a training DVD, training material (e.g. a multifunctional latex band and training rings to enhance finger and underarm power), as well as psychoeducational material explaining the link between physical activity and mood. Participants are instructed to engage in the training program on their own at home approximately three times a week for the study period of 10 weeks. They receive reminders via e-mail to motivate them to keep on exercising. At the midpoint of the intervention (5 weeks), they are sent additional motivational material via postal mail. After 10 weeks, participants are asked how often they conducted the exercises. After the second measurement point, former EP participants are offered the opportunity to participate in a subsequent 10-week bouldering group, which follows the same treatment plan as the BPT group.

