### Data quality management

All of the therapists and interviewers involved in the study are thoroughly trained for their respective tasks at the study’s headquarters. Therapists and interviewers constantly remain in close contact with the study’s headquarters and discuss all upcoming questions and therapeutic progress in regular appointments. For questions or to eliminate uncertainties, the study headquarters’ staff can be contacted anytime during the entire study period. Treatment adherence is documented in protocol assessment surveys, which are filled out by the therapists after each session (e.g. deviations from the manual, severe adverse events, and other extraordinary events). To obtain evidence of the inter-rater reliability of the SIGMA, 5% of the pre- (t0) and 5% of the post- (t1) intervention data are being collected with the participation of a second person who is observing. The quality of the data is guaranteed by strict data monitoring at the study’s headquarters over the entire period of data collection.

The patient information sheet contains a data protection declaration that is in accordance with European and German data protection laws. Sensitive data collected during the telephone interviews is pseudonymised and stored in password-protected devices. Names and addresses of the participants are recorded separately and password-protected. Patient information sheets and the screening questionnaires are stored in a locked steel cabinet. Only members of the study team have access to the lists of the names and codes of participants. No published material will contain patient identifying information.

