Participants in the BPT group have a slight risk of injuries, but this risk does not exceed the risks of other physical activities. A study on injuries in sport-climbing (which has higher risks of severe injuries than bouldering) with about 2000 climbers revealed an average number of 0.2 injuries per 1000 h of climbing [72]. In our study, participants boulder for a maximum of 10*2 h in total. In our pilot study [33, 34], no SAEs in the BPT occurred in around 2400 bouldering hours. Thus, no serious injuries are expected. Nevertheless, SAEs such as strains, ligament ruptures, or fractures as well as suicidal attempts or actual suicides are documented by the therapists for each group and interim analyses of SAEs will be performed on a regular basis. If any analyses show a cumulation of SAEs in the BPT, being significantly higher than in the CBT and the EP group, the DMSB will be consulted.. If a causal connection with the intervention can be plausibly established, the BPT will be terminated and all patients will be offered CBT instead. In addition, accident insurance is being included in the trial participation for all patients. In case of physical injuries during the BPT sessions, the affected person will be stopped from bouldering and sent to an appropriate specialist for medical clarification. Suicidal thoughts between two sessions should be shortly debriefed with the participant prior to the beginning of the session and a suicidal assessment should be carried out to decide whether the participant can distance him- or herself from suicidal tendencies. In case of a suicidal attempt, the participant will be hospitalized and excluded from the study.

All participants are asked to sign an anti-suicide contract for the duration of the study in the screening questionnaire. Interested persons who are not willing or able to complete the anti-suicide contract are not included in the study but are redirected to other treatment options with higher intensity (e.g. inpatient treatment). During the therapies, all therapists follow good clinical practice in monitoring for suicide risk, and suicide risk management plans in cases of acute risk are established by the study centre.

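### The stated route for recording SAEs cannot work in the EP arm, yet SAEs in BPT are to be compared with SAEs in EP

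*Protocol article*

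**What the plan says.** The Discussion section of the protocol article lists strains, ligament ruptures, fractures, suicide attempts and suicides as SAEs and says they "are documented by the therapists for each group and interim analyses of SAEs will be performed on a regular basis". The safety board (DMSB) is to be consulted if SAEs accumulate in BPT to a level significantly above the CBT and EP groups. BPT is stopped only if a causal link with the intervention is also plausible.

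Data quality management gives the instrument: "Treatment adherence is documented in protocol assessment surveys, which are filled out by the therapists after each session". The survey's listed contents are "deviations from the manual, severe adverse events, and other extraordinary events".

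Two other sections describe EP differently. Study design and setting says two therapists carry out each intervention, "with the exception of the EP, which is supervised by the study’s headquarters". Exercise program (EP) says: "Participants are instructed to engage in the training program on their own at home approximately three times a week". The stated contacts with EP participants before the second interview are e-mail reminders ("They receive reminders via e-mail to motivate them to keep on exercising"), one posting at week 5, and a question after 10 weeks about how often they exercised.

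**The concern.** The article names who records SAEs, on which form and when, and claims that this covers every group. For one of the three arms that person and that occasion do not exist. This is therefore a conflict within the text, not merely a detail left to a fuller document.

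Two things are at stake. First, EP participants are depressed, train unsupervised and meet no therapist during treatment. An injury or suicide attempt among them has no stated path into the SAE count. Second, EP is one of the two comparators in the monitoring rule. If BPT events are recorded at weekly sessions and EP events are not, BPT can look worse than EP when the true risks are equal.

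**Working it through.** **1. The passages side by side**

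| | BPT | CBT | EP |
|---|---|---|---|
| Therapists | two per group | two per group | none (headquarters) |
| Sessions in 10 weeks | 10 | 10 | 0 |
| Therapist survey occasions for SAEs | 10 | 10 | 0 |
| Telephone interviews (t0, t1, follow-ups) | yes | yes | yes |

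The interviews reach all arms. Their listed content includes inpatient treatment and, through the MADRS, suicidal thoughts in the last week. Injuries and suicide attempts are not listed, the interviews are not named as an SAE source, and the first one after baseline comes only at the end of treatment.

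**2. What the documents allow to be computed**

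There is no SAE rate, SAE threshold or capture fraction to reproduce. The only rate is the cited sport-climbing figure of 0.2 injuries per 1000 h. With at most 20 h per patient and 69 BPT patients, that gives 69 × 20 × 0.2 / 1000 = 0.276 expected injuries. It does not cover suicidal events, for which no rate is given.

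**3. Illustration under assumptions**

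Inputs from the article: BPT 69, CBT 69 and EP 61 (Sample size estimation), and significance level 0.05 (Data analysis). Assumptions: the same true SAE risk p in all arms, full capture in BPT and CBT, a captured fraction c in EP, and a two-sided Fisher test.

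P(false BPT > EP signal) = Σ over b, e of Bin(b; 69, p) × Bin(e; 61, p·c) × 1[b/69 > e/61 and Fisher p < 0.05]

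At p = 10% the expected recorded events in BPT are 69 × 0.10 = 6.9. In EP they are 61 × 0.10 × c = 6.1, 3.1 or 0 for c = 100%, 50% or 0%.

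| Assumed risk p | c = 100% | c = 50% | c = 0% |
|---|---|---|---|
| 3% | 0.3% | 0.7% | 1.7% |
| 5% | 0.9% | 3.6% | 13.1% |
| 10% | 1.6% | 12.9% | 70.0% |

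Check of the last column: with no EP events recorded, 6/69 against 0/61 gives p = 0.029 and 5/69 against 0/61 gives p = 0.060. Significance therefore needs at least 6 BPT events, and P(Bin(69, 0.10) ≥ 6) = 70.0%.

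The same step with 80 per arm: 6/80 against 0/80 gives p = 0.028 and 5/80 against 0/80 gives p = 0.059.

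**4. The trigger as worded**

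If BPT must be significantly above CBT and above EP separately, the false trigger at p = 10% is 0.2%, 0.7% and 1.3% for c = 100%, 50% and 0%. The equally recorded CBT arm caps it.

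If the rule means the two control arms pooled, BPT (69) is tested against 69 + 61 = 130 patients. The recorded control count is then the sum of Bin(69, p) and Bin(61, p·c). The same summation gives 2.0%, 6.9% and 19.5% at p = 10%.

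**The case against.** The strongest reply is that silence is not zero capture. The article says SAEs are documented for each group, headquarters supervises EP and a safety board oversees SAEs, and an article may leave the EP reporting line to the full protocol. Part of this stands: a reader might infer that the EP count is zero by construction, and the documents do not support that. Headquarters may collect EP events by a route the article does not state. What the reply does not remove is that the route the article does state cannot operate in EP.

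A reader might also infer that BPT could be stopped wrongly because of this. The text does not support that either. The rule names CBT as well as EP, BPT and CBT are recorded in the same way, the first consequence is only consultation, and termination needs a plausible causal connection. The error runs towards a false alarm. The protection from CBT is weaker if the two control arms are pooled, and the wording does not settle which reading is meant.

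The illustrative counts are high. Six injuries among 80 patients would be about 19 times the 0.32 that the cited rate implies (80 × 20 × 0.2 / 1000), and six is the smallest count that reaches significance against zero. This objection stands in full for the magnitude.

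It would likewise go too far to say that suicidality in EP is unmeasured, since the blinded interview rates suicidal thoughts in all arms. Patients who drop out but remain available are also interviewed. But these interviews come at t1 or later, and neither suicide attempts nor injuries appear among their listed items.

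Finally, the analysis section plans no comparative safety endpoint, so the point concerns monitoring and the reading of SAE counts, not the efficacy results.

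**Conclusion.** The point holds in a limited form. The sections on safety, data quality, design and EP contradict each other on who records SAEs in EP, and no workable route for that arm is stated. Under the stated route, EP events would be under-recorded during treatment. Harm in EP could be missed, and the BPT–EP comparison would be tilted against BPT. BPT versus CBT is largely unaffected.

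The size of the bias is not derivable. The percentages above rest on assumed risks and capture fractions and show only how the tilt behaves: negligible if SAEs are very rare, large for BPT versus EP if they are common and EP capture is poor. With separate comparisons required, false triggers stay at about 1% or below in the cases shown. The main reason to act is uncounted EP events and an unreliable BPT–EP safety comparison. The point merits correction as a cheap improvement to safety monitoring.

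**What to change.** Reconcile the four sections by stating one SAE route that is the same in all arms: the same question at the same time points in BPT, CBT and EP, including patients who have stopped attending. Existing contacts are enough. The question can be put at the end of the t1 and follow-up interviews, once the MADRS has been scored, or asked by headquarters. If an earlier time point is wanted for the regular interim SAE analyses, headquarters can ask it in all three arms. Base the between-arm SAE comparison on this common source and treat therapist reports as supplementary. State also whether BPT is compared with CBT and EP separately or pooled.

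The cost is one or two added questions. The downside is that an answer may disclose allocation to a blinded interviewer. Asking after the ratings, or through headquarters, deals with this.

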### Data analysis

The data analyses will be performed with the “IBM SPSS Statistics 21” software. In order to be able to assess the quality of the randomisation, the baseline data from the intervention and control groups will be examined for statistically significant differences. All data will be checked for plausibility. Patients who drop out of the study but are still available for the telephone interviews are being interviewed subsequently. A missing data evaluation will be carried out, and missing values will be imputed by EM-Imputation [62]. The main outcome criterion is severity of depression assessed by the MADRS. The primary data analytic strategy is “per protocol” for the superiority trial and “intention to treat” for the non-inferiority trial [63]. As a sensitivity analysis, an additional analysis with “intention to treat” for hypothesis 1 and “per protocol” for hypothesis 2 will be performed. The level of statistical significance is set at *p* = 0.05.

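### The only stated trigger for consulting the board about serious events in BPT is a statistically significant excess, which rare harm would seldom reach

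*Protocol article*

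**What the plan says.** The Discussion of the protocol article says that therapists document SAEs in each group and that "interim analyses of SAEs will be performed on a regular basis". Its examples of SAEs are strains, ligament ruptures, fractures, suicide attempts and suicides. The condition for going to the board is that SAEs accumulate in BPT, "being significantly higher than in the CBT and the EP group, the DMSB will be consulted". The next step is: "If a causal connection with the intervention can be plausibly established, the BPT will be terminated". The remaining safeguards there concern the individual: an injured participant stops bouldering and sees a specialist, suicidal thoughts are assessed, and a participant who attempts suicide is hospitalised and leaves the study.

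Under Study design and setting, the article says more generally that the board "supervises study conduction and severe adverse events (SAEs").

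Two figures support the expectation that serious injuries will not occur: sport climbing showed "an average number of 0.2 injuries per 1000 h of climbing", and in the pilot study "no SAEs in the BPT occurred in around 2400 bouldering hours".

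**The concern.** A significance test is a poor gatekeeper for rare harm. When less than one event is expected, several serious injuries can occur in one arm and none in the others without p falling below 0.05. The text nevertheless makes that result the stated condition for consulting the board, and it places the judgement of causality and the decision to end BPT after that step. This fits poorly with a board whose role is to supervise SAEs.

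If the rule were followed as written, a several-fold excess of serious harm in BPT would often not meet it. It would do so least at the early looks, when acting would protect the most patients. Nothing in the individual-level safeguards brings the board in or looks for a pattern across arms.

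**Working it through.** **Inputs**
- Enrolment: the sample size section gives 61 + 69 + 69 = 199 patients, and 199 × 1.2 = 238.8, hence 239. Equal allocation is assumed: 239 / 3 ≈ 80 per arm.
- Exposure: at most 10 × 2 h = 20 h per BPT participant (Discussion).
- Cited injury rate: 0.2 per 1000 h (Discussion).
- Significance level: 0.05, the general level in the Data analysis section, assumed to apply to SAEs.
- The article does not name the test or its sidedness, or say whether CBT and EP are compared separately or pooled. I use Fisher's exact test and report three readings: pairwise two-sided / pairwise one-sided / pooled.

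**Expected injuries in BPT at the cited rate**

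80 × 20 h = 1600 h, and 1600 × 0.2 / 1000 = 0.32.

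**Smallest BPT count that reaches significance**

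With no comparator events, the one-sided pairwise p-value for k events at n per arm is C(n,k) / C(2n,k), and the two-sided value is twice that. Against pooled comparators it is C(n,k) / C(3n,k).

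| BPT v comparator | 80 per arm | 40 per arm |
|---|---|---|
| 4 v 0, pairwise | 0.120 two-sided, 0.060 one-sided | 0.116, 0.058 |
| 5 v 0, pairwise | 0.059 two-sided, 0.029 one-sided | 0.055, 0.027 |
| 6 v 0, pairwise | 0.028 two-sided | 0.026 |
| 2 v 0, pooled | 0.110 | 0.109 |
| 3 v 0, pooled | 0.036 | 0.035 |

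The minimum is 6 / 5 / 3 events at both sizes. Four BPT injuries against none in either comparator would therefore not meet the condition on a pairwise reading.

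One event in a comparator arm, at 80 per arm, raises the minimum to 8 / 7 / 4: 8 v 1 two-sided p = 0.034; 7 v 1 one-sided p = 0.032; 4/80 v 1/160 p = 0.044.

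**Probability of reaching the trigger**

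Poisson tail probability that the BPT count reaches the minimum:

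| Situation | Mean | Pairwise two-sided | Pairwise one-sided | Pooled |
|---|---|---|---|---|
| Full sample, 5 × cited rate | 5 × 0.32 = 1.6 | 0.6% | 2.4% | 22% |
| Full sample, 10 × | 3.2 | 11% | 22% | 62% |
| Halfway, 5 × | 0.8 | 0.02% | 0.14% | 4.7% |
| Halfway, 10 × | 1.6 | 0.6% | 2.4% | 22% |
| Full sample, 10 ×, one comparator event | 3.2 | 1.7% | 4.5% | 40% |

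Full binomial enumeration at 80 per arm gives nearly the same: 2% v 0% yields 0.5% / 2.2% / 21.6%, and 4% v 0% yields 10.1% / 21.6% / 62.5%.

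**What the pilot can exclude**

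With zero events in 2400 h, the one-sided 95% upper bound is −ln(0.05) / 2400 = 1.25 per 1000 h, and 1.25 / 0.2 ≈ 6.2. Even if the cited rate held exactly, zero events would be seen with probability exp(−2400 × 0.0002) = exp(−0.48) = 62%. The pilot therefore leaves open rates at which the trigger would usually stay silent.

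**The case against.** **General oversight.** The Methods give the board supervision of SAEs without any condition, and the Discussion says what happens if there is a significant excess, not only if. The sentence may describe an escalation step that runs beside ordinary oversight. This stands in part: there is no strict contradiction, and the board may see events anyway. But no other route to it is stated. If it does see every SAE, the significance condition serves no purpose.

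**Detail left to other documents.** The choice of test and the reporting route belong in a fuller protocol or board charter. That is right, and the missing test is not the complaint. The complaint is the condition that the article does state.

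**The rate.** The 0.2 per 1000 h counts injuries in an outside study whose definition is not shown, while the trial's SAE list includes strains and suicidal events. This limits the multiples above, and also the comparison of the pilot bound with that rate. If SAEs affected 10% of BPT patients and no comparator patients, the trigger would be reached with probability 82% / 91% / 99%. The weakness therefore concerns rare harm.

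**Repeated looks.** Regular interim looks could raise the overall chance of a signal. With no comparator events, however, the BPT count only accumulates, and the minimum is the same at 40 and at 80 per arm, so a halfway look adds nothing to the full-sample probabilities. Looks taken before a comparator event occurs could help somewhat.

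**Timing.** The registration table lists recruitment as complete, so some of the benefit of early action may have passed for this trial.

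**Conclusion.** The concern holds. As written, the one stated condition for consulting the board about BPT is insensitive to a materially raised rate of rare serious harm on both pairwise readings, and only moderately sensitive when the comparators are pooled. Even the pooled reading misses a fivefold rise about 78% of the time (100% − 22%).

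This rests on about 80 per arm, full exposure of 20 h, Fisher's exact test at 0.05, no comparator events unless stated, and the cited injury rate as reference. The article gives no rate for suicidal events, so the figures do not describe all SAEs. The board's general role lessens the likely consequence. It is a change that should be made, mainly because it protects patients at almost no cost.

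**What to change.** Delete the significance condition from the Discussion. State instead that documented SAEs go to the board as they occur, or at each regular interim review, with counts by arm shown descriptively and with exact confidence intervals. The board then judges whether a causal link is plausible and whether BPT should end, which matches its role under Study design and setting.

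If a numerical prompt is wanted in addition, a simple BPT count works better than a test. With the same Poisson means, consulting at two or more injuries would fire with probability 4% at the cited rate, 48% at five times and 83% at ten times.

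The cost is a change of wording and the forwarding of reports that therapists already complete to a board that already exists.

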## Abbreviations

ADHD: Attention deficit hyperactivity disorder
BMI: Body mass index
BPT: Bouldering psychotherapy
CATI: Computer-assisted telephone interview
CBT: Cognitive behavioural therapy
EM-Imputation: Imputation using an expectation maximization algorithm
EP: Exercise program
EQ-5D: EuroQol Five Dimension Questionnaire
FERUS: Questionnaire on Resources and Self-Management Skills
FKB-20: Body Image Questionnaire
GAD-7: Generalized Anxiety Disorder 7
GSE: General Self-Efficacy Scale
HRQoL: Health-related quality of life
MADRS: Montgomery-Asberg Depression Rating Scale
PHQ-9: 9-Item Patient Health Questionnaire
R-SES: Rosenberg Self-Esteem Scale
SAE: Severe adverse events
SCL-90: Symptom-Checklist
SD: Standard Deviation
SIGMA: Structured interview guide for the Montgomery-Asberg Depression Rating Scale
UIAA scale: Scale of difficulty of the Union Internationale des Associations d’Alpinisme (International Union of the Alpine Associations)
VAS: Visual analogue scale
